### Analysis

During rounds, scores (1–9) will be calculated as a percentage of the total responses. The final responses will be analysed for each of the three study groups. We will define consensus for outcome inclusion in the COS as >70% of responses rating the outcome at 7 or greater and not more than 15% of responses rating the outcome <3 [14]. We will explore similarities and differences across the three COS generated by the different feedback methods. As there is no gold standard for feedback, all three COS will be brought forward to the consensus meeting for consideration and discussion, and for the preparation of a final COS.

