### Consensus meeting

Following completion of the Delphi, we will invite representatives of stakeholder groups from the Delphi panel, COMET Initiative and the InFACT Outcomes Working Group to the consensus meeting. To promote wide dissemination, we also will invite editors from key journals (for example, *American Journal of Respiratory and Critical Care Medicine*, *Critical Care Medicine*, *British Medical Journal*, *The Lancet*, *Intensive Care Medicine*, *Critical Care*) and funders of critical care trials. The purpose of the consensus meeting is threefold, with the common aim of reaching a consensus among those present on the content of a core outcome set for mechanical ventilation. A report from this meeting will be written up and published.

As described in the paper, participants with differing professional backgrounds in the Delphi study will be randomised into one of three groups, each using a different feedback mechanism between rounds. Therefore, the Delphi will produce three separate proposals for the variables to include in the COS. It is likely that there will be overlap between these three sets but they may also differ in regard to the outcome variable types that they contain. However, given that there is no gold standard in Delphi studies for the best feedback mechanism to attain consensus, we cannot be sure that the consensus on a COS reached by any particular group is superior to that reached by another of the groups, using a different feedback mechanism. The research team will review the consistency or variance between the three COS. If there is consistency, then one COS will be brought to the meeting, but if there is variance we will bring this to the attention of the meeting for discussion and agreement on choosing one particular COS. This is the first purpose of the meeting.

The aim of the Delphi study is only to determine ‘what’ outcomes should be measured in mechanical ventilation trials – it is not designed to determine ‘how’ the outcomes should be measured or, specifically, the time point at which the outcome should be determined. So, the second purpose of the consensus meeting is to bring together experts in mechanical ventilation trials alongside representatives of other organisations contributing to the development and/or dissemination of core outcome measure sets, including OMERACT, InFACT and COMET, to discuss ‘how’ the outcome variables in the COS should be measured.

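### The Delphi Analysis and Consensus meeting sections give different rules for turning the three arm-specific outcome sets into the final COS

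*Protocol article*

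**What the plan says.** Participants are randomised after round 1 to one of three feedback methods, stratified by stakeholder type (Randomisation). Final responses are analysed within each arm. An outcome reaches consensus if more than 70% of scores are 7 or above and no more than 15% are below 3 (Analysis, Delphi study).

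On the next step, the Delphi Analysis section notes that no feedback method is a gold standard and states that "all three COS will be brought forward to the consensus meeting for consideration and discussion". A final COS is then to be prepared from them.

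The Consensus meeting section says that "the Delphi will produce three separate proposals for the variables to include in the COS", and adds that "we cannot be sure that the consensus on a COS reached by any particular group is superior" to another's. It then puts a review before the meeting: "The research team will review the consistency or variance between the three COS". Two branches follow. Under the first, "If there is consistency, then one COS will be brought to the meeting". Under the second, where the sets vary, the attendees are told of the differences and are asked for "discussion and agreement on choosing one particular COS".

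**The concern.** The primary aim is the COS itself (Aims and research questions), so the rule that converts the Delphi results into the final set should be single and fixed in advance. The two sections differ on two things:

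- **What reaches the meeting:** all three sets always, or one set if the research team finds consistency. This article states no criterion for consistency.
- **What the meeting does with them:** prepares a final set from the three, or agrees on one of them.

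If one arm's list were adopted whole, an outcome that met consensus in the other two arms, and in the panel as a whole, could be lost because the chosen arm narrowly missed the threshold. An outcome could equally enter because only the chosen arm passed it.

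**Working it through.** **Comparing the rules.** The plan gives no figure to reproduce, so the first check is textual. There are four possible situations:

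1. The three sets are identical. Bringing one or three gives the same content, so there is no conflict.
2. The sets differ but are judged consistent. The Analysis section shows the meeting three sets; the Consensus meeting section shows it one. The rules diverge.
3. The sets differ, this is reported, and the meeting adopts one arm's set. This departs from preparing a final set out of all three. The rules diverge.
4. The sets differ, this is reported, and the meeting composes a single set from all three. The rules agree.

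So the conflict bites in situations 2 and 3.

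**Size, as an illustration.** Inputs from the article: three arms and the threshold of more than 70% scoring 7 or above. Assumptions: equal arms (no allocation ratio is stated), 50 per arm (Panel size and recruitment sets no target), the same true proportion p in every arm, independent responses, and the 15% criterion ignored.

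- Standard error at p = 0.70, from √(p(1−p)/n): one arm, √(0.21/50) = 0.065; all 150, √(0.21/150) = 0.037. The ratio is √3 = 1.73.
- Passing needs at least 36 of 50, or at least 106 of 150. The exact binomial gives:

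| True p | One arm of 50 passes | All 150 pass | Wrong side: one arm | Wrong side: combined |
|---|---|---|---|---|
| 0.60 | 0.054 | 0.004 | 5% | 0.4% |
| 0.65 | 0.188 | 0.084 | 19% | 8% |
| 0.70 | 0.447 | 0.469 | – | – |
| 0.75 | 0.748 | 0.905 | 25% | about 10% |
| 0.80 | 0.939 | 0.998 | 6% | 0.2% |

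Below 0.70 the error is passing; above it, failing (1 − 0.748 = 0.252; 1 − 0.905 = 0.095).

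- Chance that the arms disagree on an outcome when feedback does nothing, with q the one-arm pass probability: 1 − q³ − (1−q)³. At p = 0.75 and q = 0.748 this is 1 − 0.419 − 0.016 = 0.565, about 57%.
- Sensitivity to arm size at p = 0.75: 66% with 30 per arm and 38% with 100. At p = 0.80 it falls from 34% with 30 per arm to 3% with 100.

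Under these assumptions, a few outcomes near the threshold are enough to make differing sets likely even without a feedback effect.

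**The case against.** The strongest reply is that this is loose wording. The same section gives the meeting's purpose as agreement by the attendees on what the COS contains, and the Analysis section speaks of preparing a final set. In that light, choosing one COS may simply mean ending with one. This reading is tenable, but the sentence follows directly on three separate proposals and does not state it. If it is intended, the text should say so.

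A reader might infer three stronger points that the document does not support:

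- **That two thirds of the panel's ratings are discarded.** This fits only final-round scores, and only on the literal reading. Round 1 precedes randomisation, and outcomes suggested in it may be added for everyone. Group 1 sees feedback from the whole panel and group 3 from every stakeholder group. Panel representatives also attend the meeting.
- **That the section contradicts its own statement that no arm can be taken as superior.** That uncertainty is a fair reason to give the decision to a meeting. It sits awkwardly with adopting one arm's list, but it is not a contradiction.
- **That chance at the 70% line is caused by using one arm.** Any cutoff behaves this way; at a true rate of 70% the pass probability is 0.45 for one arm and 0.47 combined.

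Two further objections carry weight. Panellists are nominated and rescore after feedback, so an independent binomial model with one common rate is only a rough guide. A criterion for consistency may also stand in a fuller protocol, so its absence here is not itself a fault. Neither removes the difference between the two sections.

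**Conclusion.** The two sections give different rules for forming the final COS, and this should be corrected. They lead to different results only if sets that are not identical are called consistent, or if the meeting adopts one arm's set whole. In the second case the final set would rest on about one third of the final-round scores, a share inferred from three arms of intended equal stakeholder representation.

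For an outcome with a true rate of 65% or 75%, the excess misclassification from using one arm of 50 rather than all 150 is about 10 to 16 percentage points (18.8 − 8.4 = 10.4; 25.2 − 9.5 = 15.7). These figures depend on assumed arm sizes and the simplified model, and show scale only. The textual conflict does not depend on them. It warrants correction before the Delphi begins but does not invalidate the design.

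**What to change.** State one rule in both sections:

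- Always bring the results of all three arms to the meeting, in a table giving for each outcome the percentage scoring 7 or above and the percentage scoring below 3, by arm and for all arms combined, against the stated consensus criteria.
- Have the meeting decide outcome by outcome where the arms disagree.
- Remove or reword "discussion and agreement on choosing one particular COS" so that the final set may draw on all arms, and drop the option of bringing only one set.

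The voting procedure is for the investigators to choose. The cost is some rewording, one extra table and a slightly longer agenda. The Study status section says the Delphi has not begun, so the rule can be settled before any results are seen.

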### Ethical requirements

Individual participants will be approached (or will self-volunteer) after nomination by an organisational lead from an organisation with which they are affiliated. Participants will be sent a short introductory email with an information sheet about the study, including details of randomisation, explicit details about what will be involved and asked for their consent to participate. Participants will be given the option to withdraw from the study at any time. This study will be conducted entirely online and consistent with standard practice in survey research; consent will be assumed by agreement to participate and completion of online questionnaires. The study was reviewed and approved by the School of Medicine, Dentistry and Biomedical Science Research Ethics Committee at Queen’s University Belfast (QUB), Northern Ireland, UK, in October 2014 [Ref: 14.34v2] (Ethics Committee Reference). Sponsorship and indemnity is provided by QUB.

### Consensus meeting

Following completion of the Delphi, we will invite representatives of stakeholder groups from the Delphi panel, COMET Initiative and the InFACT Outcomes Working Group to the consensus meeting. To promote wide dissemination, we also will invite editors from key journals (for example, *American Journal of Respiratory and Critical Care Medicine*, *Critical Care Medicine*, *British Medical Journal*, *The Lancet*, *Intensive Care Medicine*, *Critical Care*) and funders of critical care trials. The purpose of the consensus meeting is threefold, with the common aim of reaching a consensus among those present on the content of a core outcome set for mechanical ventilation. A report from this meeting will be written up and published.

As described in the paper, participants with differing professional backgrounds in the Delphi study will be randomised into one of three groups, each using a different feedback mechanism between rounds. Therefore, the Delphi will produce three separate proposals for the variables to include in the COS. It is likely that there will be overlap between these three sets but they may also differ in regard to the outcome variable types that they contain. However, given that there is no gold standard in Delphi studies for the best feedback mechanism to attain consensus, we cannot be sure that the consensus on a COS reached by any particular group is superior to that reached by another of the groups, using a different feedback mechanism. The research team will review the consistency or variance between the three COS. If there is consistency, then one COS will be brought to the meeting, but if there is variance we will bring this to the attention of the meeting for discussion and agreement on choosing one particular COS. This is the first purpose of the meeting.

The aim of the Delphi study is only to determine ‘what’ outcomes should be measured in mechanical ventilation trials – it is not designed to determine ‘how’ the outcomes should be measured or, specifically, the time point at which the outcome should be determined. So, the second purpose of the consensus meeting is to bring together experts in mechanical ventilation trials alongside representatives of other organisations contributing to the development and/or dissemination of core outcome measure sets, including OMERACT, InFACT and COMET, to discuss ‘how’ the outcome variables in the COS should be measured.

The third purpose of the consensus meeting is to invite editors from prominent critical care journals to contribute, particularly to discussions on dissemination of the core outcome set on mechanical ventilation.

### Observational cohort study

We will conduct a prospective observational cohort study to determine if participation of trial investigators in the Delphi panel increases COS uptake in comparison with investigators who did not participate, on the basis of the use of the COS in published reports of clinical trials in the decade after the COS is published.

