### Aims and research questions

The primary aim is to develop a COS for trials involving patients undergoing mechanical ventilation where an aim of the intervention is to modify time spent on mechanical ventilation. The secondary aims are to determine the most valid method of gaining consensus for a COS, and to evaluate the COS uptake 5 and 10 years after its publication.

Our research questions are:Which outcomes are ranked by stakeholders as critical for inclusion in the COS?How is the ranking process influenced by the method of stakeholder group feedback during Delphi rounds?Do Delphi panel participants rank the importance of outcomes differently depending on their knowledge of the other groups’ ranking?Does participation by investigators in the Delphi panel affect their subsequent use of the COS, compared with investigators who do not participate?

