## Methods

Study authors will be randomised to either participate in the Delphi panel as a ‘trial investigator’ stakeholder representative or not to participate (see Fig. 2). As we are using data available in the public domain, informed consent will not be sought from those not involved in the Delphi. Participants involved in the Delphi will be asked for informed consent in accordance with other participating stakeholder groups.

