### Analysis

The primary outcome is the number and proportion of authors who have used the COS in trials reported at 5 and 10 years after the publication of the COS. Data will be compared between groups using the chi-square test. A *P* value <0.05 will indicate a statistically significant difference.

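### The uptake study randomises authors but is labelled observational and worded as participants versus non-participants; the primary comparison should be stated as by randomised allocation

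*Protocol article*

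**What the plan says.** The opening Methods section and the section headed Observational cohort study both describe the uptake component as observational. The latter gives its purpose as "to determine if participation of trial investigators in the Delphi panel increases COS uptake in comparison with investigators who did not participate". The research question under Aims and research questions has the same form: "Does participation by investigators in the Delphi panel affect their subsequent use of the COS, compared with investigators who do not participate".

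The Methods section that follows Sample identification describes a different design: "Study authors will be randomised to either participate in the Delphi panel as a ‘trial investigator’ stakeholder representative or not to participate". The caption of Fig. 2 combines both ideas, referring to randomisation within the observational cohort; the figure itself is not available to us.

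The same Methods section seeks consent from authors who enter the Delphi and not from the comparison authors, whose data are public. Under Ethical requirements, consent is inferred from agreeing to take part and completing the questionnaires, and withdrawal is allowed at any time.

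The primary outcome is the number and proportion of authors who used the core outcome set (COS) at 5 and 10 years. On the test, the Analysis section says only: "Data will be compared between groups using the chi-square test", at the 0.05 level.

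**The concern.** A comparison of randomised arms and a comparison of participants with non-participants are different analyses. The first supports a causal answer with an unadjusted test. In the second, an unadjusted chi-square has no protection against confounding.

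The two coincide only if every author allocated to the Delphi takes part, and the consent and withdrawal provisions make that unlikely. The section on panel size also plans reminders and other measures against attrition. Authors who accept may well be those already interested in core outcome sets, and the same interest plausibly makes them more likely to use the COS later. An analysis that follows the aim as worded could then credit participation with a difference that existed before anyone was invited.

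What is at stake is the answer to the fourth research question, which the Discussion frames causally, as whether participation increases use of the COS.

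**Working it through.** The article gives no sample size, acceptance rate or expected uptake for this component, so there is no planned figure to reproduce. The check has two parts.

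**1. The text side by side**

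| Section | What it fixes |
|---|---|
| Methods (opening) | Observational design |
| Observational cohort study | Observational design; contrast by participation |
| Aims and research questions | Contrast by participation |
| Methods (after Sample identification) | Random allocation to Delphi or no Delphi; consent sought on the Delphi side only |
| Analysis (after those Methods) | Chi-square between groups; groups not defined |

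The design label and the contrast point one way and the allocation points the other. The only sentence on the test fits either. No passage says that authors are analysed in the arm to which they were allocated.

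**2. Illustration of what depends on the choice**

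All rates here are assumptions, not taken from the documents. Allocation is 1:1 and participation has no true effect. Let *a* be the proportion who accept, *pw* the later uptake in authors who would accept, *pu* the uptake in those who would decline, and *d* = *pw* − *pu*.

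- By allocation: both arms have uptake *pu* + *a·d*, so the expected difference is 0.
- Decliners dropped: *pw* − (*pu* + *a·d*) = (1 − *a*)·*d*.
- Decliners counted as non-participants: their pooled uptake with the control arm is [(*pu* + *a·d*) + (1 − *a*)·*pu*]/(2 − *a*). The difference is 2(1 − *a*)·*d*/(2 − *a*).

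The spurious difference depends only on *a* and *d*, not on the level of uptake.

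Worked case: *a* = 0.5, *pw* = 0.30, *pu* = 0.10. By allocation, both arms are at 0.20. With decliners dropped, 0.30 − 0.20 = 0.10. With decliners counted as non-participants, (0.20 + 0.5 × 0.10)/1.5 = 0.167, so the difference is 0.30 − 0.167 = 0.133.

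| *a* | *d* | By allocation | Decliners dropped | Decliners counted as non-participants |
|---|---|---|---|---|
| 0.3 | 0.10 | 0 | 7.0 points | 8.2 points |
| 0.5 | 0.10 | 0 | 5.0 | 6.7 |
| 0.7 | 0.10 | 0 | 3.0 | 4.6 |
| 0.3 | 0.20 | 0 | 14.0 | 16.5 |
| 0.5 | 0.20 | 0 | 10.0 | 13.3 |
| 0.7 | 0.20 | 0 | 6.0 | 9.2 |

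Rejection rates also depend on the number of authors and the uptake level. Take the worked case with 100 per arm and decliners counted as non-participants. That gives 50 participants against 150 others, with pooled uptake 0.20. The standard error is √[0.16 × (1/50 + 1/150)] = 0.0653 under the null and √(0.21/50 + 0.139/150) = 0.0716 under the two rates. The rejection probability is Φ[(0.1333 − 1.96 × 0.0653)/0.0716], about 53%.

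With *pw* = 0.30, *pu* = 0.10 or 0.20, the same three acceptance rates and 100 or 200 authors per arm, the rejection rate under no effect is about 6% to 66% with decliners dropped. It is about 11% to 85% with decliners counted as non-participants. Analysis by allocation keeps the nominal 5%.

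**The case against.** The strongest reply is that no as-participated analysis is stated. The Methods section names its two arms by whether authors are to participate, so the non-participants in the aim may simply be the arm allocated not to participate. On that reading, the groups in the chi-square test are the randomised arms and nothing is lost. Fig. 2 might show where decliners go, and the handling of decliners is commonly left to an analysis plan or full protocol.

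Much of this stands. A reader might infer that the plan discards its randomisation and builds in volunteer bias. The documents do not support that: no text moves decliners to the other side or drops them, and the test sentence is compatible with comparison by arm. The illustration also rests wholly on assumed rates and an assumed handling of decliners.

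The conflict itself remains. The point is not that an analysis set is undefined. The sections that give the aim describe a contrast by participation under an observational label, while the design section randomises. An analysis plan that followed the aim literally would compare self-selected groups.

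On importance, uptake is a secondary aim. Because outcomes come from published reports, every randomised author can still be analysed as allocated at 5 and 10 years, so nothing is yet irreversible.

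**Conclusion.** The article contradicts itself on the design of the uptake study and leaves open which groups its only test compares. If the comparison were made by actual participation, as the aim and research question are worded, it would forfeit the protection of randomisation and be open to volunteer bias.

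The size of that bias cannot be derived from the documents. The figure of roughly 3 to 17 points with no true effect assumes acceptance of 30% to 70%, a 10- to 20-point gap in uptake between willing and unwilling authors, and decliners either dropped or counted as non-participants. It shows why the wording matters and does not predict this study's result. If the intended comparison is already by allocation, this bias does not arise and the text only needs to say so.

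**What to change.** Describe the component as a randomised comparison in the opening Methods and in the section now headed Observational cohort study. In the research question, in that section and in its Analysis section, state that the primary chi-square comparison is by randomised allocation (Delphi versus no Delphi). All randomised authors should be in the denominator, whether or not they accepted the invitation or completed the rounds. Any comparison by actual participation should be labelled secondary.

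The change is to wording only and needs no new data, since outcomes are already to be read from published reports. The small cost is dilution. If invitation alone has no effect on those who decline, an effect of δ among acceptors appears as *a*·δ; for example, 10 points at an assumed 50% acceptance appears as 0.5 × 10 = 5 points.

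A complier-average estimate with allocation as the instrument, and a risk difference with a confidence interval, would be useful but are optional.
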